## Secondary outcomes

### Visual analogue scale

Patients will be asked to indicate their perception of pain along a 10-cm line, with 0 (no pain) on one end and 10 (worst pain) on the other end. Patients will be asked to place a mark along the line to denote their level of pain [38]. The time frame will be pre-treatment, post-treatment 10 weeks and after 3 months of follow-up.

### Neck Disability Index

The NDI is a modification of the Oswestry Low Back Pain Disability Index. It is a patient-completed, condition-specific functional status questionnaire with ten items, including pain, personal care, lifting, reading, headaches, concentration, work, driving, sleeping and recreation. The NDI has sufficient support and usefulness to retain its current status as the most commonly used self-report measure for neck pain. It may be scored as a raw score or doubled and expressed as a percentage. Each section is scored on a 0 to 5 rating scale, in which zero means ‘no pain’ and 5 means ‘worst imaginable pain’. All of the points may be summed to a total score. The test may be interpreted as a raw score, with a maximum score of 50, or as a percentage. Zero points or 0% means no activity limitations, and 50 points or 100% means complete activity limitation (English and Chinese versions of the NDI are shown in Fig. 3) [28]. The time frame will be pre-treatment, post-treatment 10 weeks and after 3 months of follow-up.

**Fig. 3 Fig3:**
[figure not shown]
Neck disability index (NDI). English and Chinese versions of the NDI

### Three-dimensional posture parameters of the head region in relation to the thoracic region

#### Instrumentation for measurement

For assessment purposes, the Global Posture System (GPS) 600 (Chinesport, Udine, Italy), as shown in Fig. 4, is a novel and unique device that is used to examine all postural variables at once [19–21]. This posture analysis system consists of a number of units and software that make it possible to acquire images for body part measurements and collect information on weight distribution, barycentre and the stability of the patient being examined; it will be used per the manufacturer’s instructions [19]. We will analyse the posture of the head in relation to the thoracic region in terms of translations and rotations.

**Fig. 4 Fig4:**
[figure not shown]
Global posture system (GPS). The GPS 600 device (Chinesport, Udine, Italy) consists of *1* software GPS 5.0, *2* desktop, *3* podostabil, *4* podata, *5* Lux postural analyzer

#### Components of GPS

Software GPS 5.0Desk topPodostabilPodataLux postural analyzer

### Assessment procedures

#### Assessment location

Any room in any place or clinic may be used for the application of GPS. No preparations are needed for the room, but the study room will have sufficient space and flat, plain-coloured walls.

#### GPS setup and operation

The GPS will be calibrated prior to measurement.

#### Preparation of patients

Patients will be asked to wear tight-fitting clothes to allow the examiners to find various anatomical sites. The examiners will place 13 markers on each patient before taking four photographs.

#### Marker placement

Antero posterior view markers. Thirteen coloured markers at anatomical locations as shown in Fig. 5.Two lateral view markers. Thirteen coloured markers at anatomical locations as shown in Fig. 5. The points over which the markers are fixed are well cleaned with alcohol to remove sweat and ensure good fixation. Four photographs or four views will be obtained for every patient: anterior and posterior views and two lateral (right and left) views.

**Fig. 5 Fig5:**
[figure not shown]
Examples of the photographs taken using the Global Posture System (GPS). **a** Anterior and posterior views. **b** Sagittal plane or lateral views. The six reflective markers used in the analysis are: acromion, anterior superior iliac spine, posterior superior iliac spine, glabella, tragus, C7 and middle sternal notch

#### Starting position of the patients

For the photographs, patients will be instructed to stand on the Lux postural analyzer part of the GPS, take a deep breath three to five times for full relaxation, nod their head up and down twice with their eyes closed and assume what they feel to be a neutral body posture. Their eyes will be open and the subject stopped from moving during this stance. Four digital photographs will be taken using a computer mouse. The set of photographs will be processed through secure software analyses using GPS.

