## Procedures

Potential patients will be recruited through advertisements in clinical waiting rooms and via mobile patient recruitment applications, like Wechat (Tencent Ltd, Shenzhen, China). Eligible patients will be 17 to 40 years of age with a history of neck pain for longer than 3 months and who are interested in taking part in a clinical trial of physical therapy. No details of radiographic features of the neck region will be mentioned in the advertisements. Volunteers will contact the project coordinator or physician of the rehabilitation clinic and will undergo an initial screening. A clinical and radiological examination will be used to exclude the presence of a specific cause of neck pain.

Patients will complete a written, informed consent form, provide demographic data and complete a survey of patient-reported outcome measures. An outcome assessor will measure the rotational movements and translational displacements of the head in relation to the thoracic region using GPS.

Following the baseline assessment, a research assistant will randomize patients to a study group and control group using sealed, numbered envelopes and a randomisation list generated by the “random integer generator” (https://www.random.org/integers/). The randomisations will be restricted to permuted blocks of different sizes. Each random permuted block will be transferred to a sequence of consecutively numbered, sealed, opaque envelopes for storage in a locked locker until required. As each patient formally enters the trial, the researcher will open the next envelope in the sequence in front of the patient. A blinded investigator will perform all outcome assessments at baseline, after 10 weeks of intervention and after 3 months of follow-up.

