### Randomization procedure

The appropriateness of the methods used to ensure the blinding of the outcome measurement assessor will be determined through post-study interviews that ask whether they were aware of the group allocation and whether they felt that the treatments were consistent.

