### Limitations of this study

The major limitation of this protocol is its non-double-blind design. However, the outcome assessors and statistical analysts will be blinded to the intervention to decrease potential bias and ensure the prominence of this trial. This study also lacks long-term follow-up observations and assessments. The follow-up evaluation will occur 3 months after completion of the 10-week intervention period, which will be an effective evaluation of short and medium periods for almost 6 months. In conclusion, the results of this study are expected to provide information on the feasibility of conducting RCT evaluations of the effect of the addition of a new, 3D adjustable CTPCO to multimodal treatment of NSNP and evaluations of the use of ambulatory mirror-image functional re-training via the wearing of a CTPCO as one of the multimodal exercises used for correcting posture in 3D directions in NSNP patients.

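### Reading the posture photographs under code at the end, with arm, visit and date hidden, would make the one outcome that assessor blinding can protect depend less on patients keeping their arm to themselves

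*Protocol article*

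**What the plan says.** All references are to the Protocol article.

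- **Who assesses.** Under Procedures: "A blinded investigator will perform all outcome assessments at baseline, after 10 weeks of intervention and after 3 months of follow-up". On posture, the same section says: "An outcome assessor will measure the rotational movements and translational displacements of the head in relation to the thoracic region using GPS".
- **When the arm becomes known.** Under Procedures: "Following the baseline assessment, a research assistant will randomize patients to a study group and control group using sealed, numbered envelopes". At that point "the researcher will open the next envelope in the sequence in front of the patient". Only the study arm then walks in the brace (Interventions).
- **How posture is captured.** Under Preparation of patients: "The examiners will place 13 markers on each patient before taking four photographs". Under Starting position of the patients, the patient adopts a stance that feels neutral, four digital photographs are taken, and "The set of photographs will be processed through secure software analyses using GPS".
- **What is measured.** The two sections on postural translations and rotations of the head define distances and angles from points that include the nose, the outer corner of the eye, the chin and the lower ear margins. For Ry, either the glabella or the nasal tip may be used.
- **Protection and check.** Limitations of this study says that "the outcome assessors and statistical analysts will be blinded to the intervention". Under Randomization procedure, assessors will be asked after the study "whether they were aware of the group allocation".
- **Use of the result.** Statistical analysis compares change scores between groups and computes Hedges-corrected effect sizes for VAS, NDI and posture to advise on the size of a full trial.

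**The concern.** VAS and NDI are completed by patients who know their treatment, so blinding an assessor cannot protect them. It can protect posture. As described, that protection rests on a person who meets each patient at 10 weeks and at 3 months, and the article mentions no instruction to patients not to disclose their arm.

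If a patient does disclose it, the reading leaves room for expectation to act. The caption of Fig. 5 names the markers used in the analysis: acromion, anterior and posterior iliac spines, glabella, tragus, C7 and sternal notch. The nose, eye corner, chin and lower ear margins are not among them, so on the text shown someone has to locate these points on the image. The choice of landmark for Ry adds to this.

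The post-study interview would show that blinding had failed, but by then the readings would be fixed. Because the measurement is taken from photographs, the reading can be separated from the visit, and nothing in the text makes use of that.

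**Working it through.** **1. Which visits can leak.** Baseline assessment precedes randomisation, so two of the three visits matter. With 24 patients and no dropout there are 24 × 2 = 48 contacts. The documents give no disclosure rate. If each contact carries an independent chance *p* (assumed), the chance of at least one disclosure is 1 − (1 − *p*)^48:

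| assumed *p* | at least one disclosure | expected number (48*p*) |
|---|---|---|
| 0.01 | 38% | 0.5 |
| 0.02 | 62% | 1.0 |
| 0.05 | 91% | 2.4 |

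Some leak is plausible even at a low rate. How many readings it would affect is unknown.

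**2. Bias in the change score.** Let *f* be the share of study-arm follow-up readings made with the arm known, and *b* the shift in SD units of the change score. Baseline was read before randomisation, so its shift is zero and the bias in the between-group effect is *f* × *b*. All values are assumed:

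- 0.10 × 0.3 = 0.03 SD
- 0.25 × 0.2 = 0.05 SD
- 0.50 × 0.4 = 0.20 SD
- no leak: 0

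**3. What that would do to a sample size based on the posture effect.** The protocol gives α = 0.05 and at least 80% power; two-sided testing and a true effect of 0.50 SD are assumed. Then *n* per arm = 2(1.96 + 0.842)² / *d*² = 15.70 / *d*², and power at the true effect is Φ(0.50 √(*n*/2) − 1.96).

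| apparent *d* | *n* per arm | power for true 0.50 |
|---|---|---|
| 0.50 | 62.8 (63) | 80% |
| 0.53 | 55.9 (56) | 75% |
| 0.55 | 51.9 (52) | 72% |
| 0.70 | 32.0 (about 32) | 52% |

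**4. Scale against chance.** With an equal split of 12 per arm (assumed), the standard error of a standardised difference is about √(2/12) = 0.41. The largest assumed bias, 0.20, is about half of that.

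**5. Why hiding the visit helps.** If a reader knows a patient's arm but not which image is baseline, any shift is expected to fall equally on baseline and follow-up images: *b* − *b* = 0 in the change score. This fails only so far as the reader can guess the order from the image. Hiding the arm alone would not have this effect.

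**6. Where the result is used.** The section Primary outcome measure limits the choice for the full trial to a patient-reported measure. Posture is not one, so step 3 bears only on the posture effect sizes listed under Statistical analysis.

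**The case against.** The strongest reply is that the article states nothing wrong here. Assessors and analysts are declared blinded, the lack of double blinding is named as the major limitation, and whether assessor blinding holds is itself a feasibility question that the pilot will test. The article does not name the reader of the photographs and speaks of examiners in the plural. Coding and reading order are details that a full protocol may well contain. This stands, and it is why the point is a suggestion.

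A second reply is that coded reading cannot do all that one might hope. This also stands. Markers are placed in person, the patient who knows the arm chooses the neutral stance, and the photographs must show the face. An assessor who has met 24 people may recognise them.

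Three stronger readings are therefore not supported:

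- A reader might infer that the blinding of posture could be guaranteed, or its dependence on patients removed. The live steps and the visible faces rule that out; only the reading step is protected.
- A reader might infer that all three visits put blinding at risk. Baseline comes before randomisation, so only two do.
- A reader might infer that the full trial would be undersized, at 52 to about 32 per arm instead of 63. Those figures rest on assumed values, and the primary outcome of that trial is to be a patient-reported measure.

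The reply does not dispose of the gap between detecting a leak and preventing its effect, nor of the judgement needed to place unmarked landmarks.

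**Conclusion.** The point holds as a low-cost improvement to a secondary outcome. On the text shown, the blinding of the posture reading rests on an investigator who meets patients aware of their arm at two visits, and the only planned check comes too late to correct a reading. Attributing the reading to that investigator is an inference from Procedures, though the natural one.

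The size cannot be taken from the documents. Under the assumptions shown, the bias runs from zero with no leak to 0.20 SD. Even the upper value is small beside the sampling error of a 24-patient pilot; the difference is that it would act in one direction. The feasibility outcomes are not affected, apart from what the assessor interview reports.

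**What to change.** - **Starting position of the patients:** state that, after the last 3-month visit, the photographs from baseline, 10 weeks and 3 months are read under a random code in random order, with arm, visit and date hidden, and that these readings supply the posture change scores. Where existing staff allow, the reader should be someone who did not assess the patients.
- **Postural rotations of head:** name one fixed landmark for Ry.
- **Baseline readings made at the visit:** keep them for entry and brace data only.
- **State the limit:** marker placement and stance remain live steps, and faces may be recognised.

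The cost is protocol wording and one re-reading of the baseline images. Posture results become available only at the end. The sample of 24 does not change.

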### Measured items (the postural parameters) of the head region in relation to the thoracic region

A right-handed Cartesian coordinate system with x-axis positive to the left, y-axis positive vertically and z-axis positive to the anterior will be used to describe postures of the head as translations or displacements in centimetres (Tx, Ty, Tz) along these axes and as rotations (Rx, Ry, Rz) in degrees from a normal upright stance. Vertical translations (Ty), which would require radiographic analysis of hypo- or hyper-lordosis, will not be calculated in the present study (Fig. 6) [13].

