### Postural translations of the head

Tx (right or left side shifting or lateral translation): measure horizontal distance from the ideal plumb line passing through middle sternal notch to vertical line passing through nose.Tz (anterior or posterior translation): measure horizontal distance from the vertical line crossing the middle acromion process to the vertical line crossing the external ear.

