### Postural rotations of head

Rx (flexion or extension position): measure angle between tragus of ear, canthus of eye and the horizontal line.Ry (right or left rotation): measure angle between glabella of forehead or tip of nose, the middle point of chin and the vertical line.RZ (right or left side bending): measure angle between the inferior margins of the right and the left ear and the horizontal line.

The time frame is pretreatment, post-treatment 10 weeks and after 3 months of follow-up.

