### Statistical analysis

Results of primary outcome measures will be provided descriptively in tables and compared to the a priori established goals. To provide a recommendation for estimated sample size for a future full-scale RCT, between-group effect sizes and 95% confidence intervals (CIs) with Hedges correction will be calculated for changes in the secondary outcomes of VAS, NDI and 3D posture parameters. The mean ± standard deviation score for each of the subscales will be used in the calculation of the effect size. Estimated sample size will be determined using the between-subject effect size, with a minimum of 80% power (*α* = 0.05). The sample size will be increased to allow for an estimated 20% dropout rate. Statistical methods for the secondary outcome measures will be evaluated via comparisons of changes between groups. Complete case analyses will be performed to include outcomes from all patients who completed baseline and follow-up evaluations, as recommended in the Consolidated Standards of Reporting Trials (CONSORT) guidelines [39]. The between-group difference in change scores for each outcome measure from baseline to follow-up will be determined and reported as the means and 95% CI, using an analysis of covariance. Covariates of age and sex will be included in the analysis. All statistical analyses will be performed in SPSS version 23.0 software (IBM Corporation, Armonk, NY) with significance set at *P* < 0.05.

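### Ry is labelled rotation but defined as a frontal-plane tilt, and the sided posture parameters (Tx, Ry, Rz) can cancel across patients if signed changes are averaged

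*Protocol article*

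**What the plan says.** All places are in the protocol article.

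- **Axes** (Measured items): "A right-handed Cartesian coordinate system with x-axis positive to the left, y-axis positive vertically and z-axis positive to the anterior". So y is vertical and z points forward. Translations are displacements along these axes, and rotations are given "as rotations (Rx, Ry, Rz) in degrees from a normal upright stance". On this system Ry is turning about the vertical and Rz is side bending in the frontal plane.
- **Sideways shift**: the rule is "Tx (right or left side shifting or lateral translation): measure horizontal distance from the ideal plumb line passing through middle sternal notch", measured to a vertical line through the nose (section Postural translations of the head).
- **Rotation** (Postural rotations of head): "Ry (right or left rotation): measure angle between glabella of forehead or tip of nose, the middle point of chin and the vertical line". The same list defines Rz, side bending, from the line between the two ears against the horizontal.
- **Sagittal parameters**: "Tz (anterior or posterior translation): measure horizontal distance from the vertical line crossing the middle acromion process" and "Rx (flexion or extension position): measure angle between tragus of ear, canthus of eye and the horizontal line". Neither has a left or right side.
- **Patients and treatment** (Inclusion criteria; Ambulatory mirror-image functional re-training): any posture abnormality on the GPS screen qualifies, with no direction required, and the brace is set against each patient's own deviation.
- **Analysis** (Statistical analysis): Hedges-corrected effect sizes "will be calculated for changes in the secondary outcomes of VAS, NDI and 3D posture parameters", computed from mean and SD, plus an analysis of covariance of change scores. The covariates named are age and sex.

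**The concern.** An outcome called rotation should respond to rotation. Ry as written responds fully to side bending and only weakly to turning, and it allows two upper landmarks that give different values for the same head position. A treatment effect on turning could be missed, and an effect on side bending could be counted twice, under Ry and under Rz.

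The coding problem is separate. A brace that works moves left-deviating patients to the right and right-deviating patients to the left. If those changes carry opposite signs and are averaged, they offset each other and also widen the SD. An effective brace could then look ineffective on Tx, Ry and Rz. 3D head posture is part of the stated hypothesis and secondary aim, and its effect sizes are listed among those calculated towards the sample-size recommendation.

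**Working it through.** The article gives no posture means, SDs, side split or face dimensions, so there is no stated figure to reproduce. The pilot size of 24 is set by citation, and nothing here depends on it. All magnitudes below are assumptions chosen to show the mechanism.

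**1. What Ry reads.** Let the upper landmark lie a height *h* above the chin point and a depth *e* in front of it. In the frontal view:

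- Pure side bend by θ: the line tilts by θ, so the reading is θ.
- Pure rotation by θ about the vertical: the sideways offset is *e* sin θ and the height stays *h*, so the reading is arctan(*e* sin θ / *h*).

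With θ = 10° (sin θ = 0.1736):

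| Upper landmark (assumed) | *e* (cm) | *h* (cm) | Rotation reads | Side bend reads |
|---|---|---|---|---|
| Same depth as chin | 0 | 11 | 0.0° | 10.0° |
| Glabella | 1 | 11 | arctan(0.1736/11) = 0.9° | 10.0° |
| Nose tip | 2 | 7 | arctan(0.347/7) = 2.8° | 10.0° |
| Nose tip | 3 | 7 | arctan(0.521/7) = 4.3° | 10.0° |

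The side bend that Ry reads in full is the movement Rz already measures from the ears.

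**2. Cancellation if signed values are averaged.** Assumed inputs: true deviation of size 2.0 (SD 0.7), measurement error SD 0.4 at each visit, 60% of the deviation corrected in the study arm and 20% in control, and a share *p* of patients deviating left.

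- Mean signed baseline: (2*p* − 1) × 2.0.
- Between-arm difference in mean change: −(0.6 − 0.2) × (2*p* − 1) × 2.0 = −0.8(2*p* − 1).
- Variance of signed baseline: V = 2.0² + 0.7² − [(2*p* − 1) × 2.0]².
- Variance of change in an arm correcting a fraction *c*: *c*²V + 2 × 0.4².
- The SD is the square root of the average of the two arm variances.

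At *p* = 0.5, V = 4.49. The arm variances are 0.36 × 4.49 + 0.32 = 1.936 and 0.04 × 4.49 + 0.32 = 0.500, so the SD is √1.218 = 1.10 and the difference is 0.

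For scale, the number per arm for 80% power at two-sided α = 0.05 (sidedness assumed) is 15.70/d², rounded up.

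| Share on left | Difference | SD | Signed d | n per arm |
|---|---|---|---|---|
| 50% | 0.00 | 1.10 | 0.00 | none finite |
| 60% | −0.16 | 1.09 | −0.15 | 728 |
| 70% | −0.32 | 1.04 | −0.31 | 168 |
| 80% | −0.48 | 0.96 | −0.50 | 64 |
| 90% | −0.64 | 0.84 | −0.76 | 28 |
| 100% | −0.80 | 0.65 | −1.24 | 11 |

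Simulation of the same set-up on absolute deviation gives a difference of about −0.78, an SD of 0.64 and d of about −1.22 (11 per arm), whatever the split.

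**3. Would adjusting for the signed baseline rescue it?** No. At an even split, a simulated analysis of covariance with signed baseline added gives an adjusted arm difference of 0.00. The benefit lies in the slope on baseline, which a common-slope model does not report as a treatment effect.

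**The case against.** The strongest reply is that the article never says signed values are averaged. The axes describe posture, the rule for Tx speaks of a distance, and right or left may be only a label. Under that reading nothing cancels, and an analysis plan that is not shown may already use absolute values. This stands: cancellation is conditional. The signed reading is nevertheless the natural one, because displacements are defined along axes with stated positive directions, and setting the brace against a deviation needs its direction.

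The size of the loss is also assumed. Full cancellation needs an even side split, which the article does not give. Patients need not deviate on every parameter either. In a related set-up (2 cm shift halved in the study arm, none corrected in control, error SD 0.5 cm), the absolute-value effect is about 1.3 if all patients deviate laterally. It is roughly 0.7 if half do and 0.5 if a third do, so there is less effect to lose.

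On Ry, the figure illustrating the measurement is not available here, the face dimensions are assumed, and the nose tip keeps some sensitivity to rotation. The written definition still conflicts with its label, and no later choice of analysis can change that.

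A reader might infer that the posture effect sizes as a whole cannot show correction. The document does not support that. Tz and Rx have no left/right sign and would offset only if patients deviate in both sagittal directions.

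A reader might also infer that the pilot's main purpose is at risk. It is not: the primary outcome is feasibility, and under Primary outcome measure the future trial's endpoint is chosen from patient-reported measures only.

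**Conclusion.** The point holds in a limited form and should be fixed.

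- **Ry**: the definition is wrong for its label. It measures mainly frontal-plane tilt, largely duplicates Rz, and depends on which permitted landmark is used. This rests on the stated axes and plain geometry; only the exact 0 to 4 degree readings rest on assumed face dimensions.
- **Tx, Ry, Rz**: if signed changes are averaged, the effect is lost fully at an even side split, partly at unequal splits (from 1.22 to 0.31 at 70:30 and to 0.76 at 90:10 under the assumptions above), and not at all when all deviations lie on one side.
- **Not affected**: VAS, NDI and the feasibility outcomes. Tz and Rx are affected only if both sagittal directions occur.

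The harm is confined to the posture secondary outcomes and can be repaired from data already planned.

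**What to change.** 1. Redefine Ry with one fixed landmark rule that responds to rotation and can be read from the four planned photographs. Left-right asymmetry of the horizontal nose-to-tragus distance in the anterior view is one candidate, to be checked for reliability first. Otherwise drop Ry from the effect-size table.
2. State that Tx, Ry and Rz are analysed as absolute deviation from neutral at each visit, with the baseline value as a covariate. Apply the same to Tz and Rx if both sagittal directions occur.
3. Add a sensitivity analysis in which each follow-up value is multiplied by the sign of that patient's baseline deviation, so that overcorrection past neutral shows as a negative value.
4. Report the number of patients deviating to each side at baseline, by arm.

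The cost is recoding of collected values and, for Ry, re-measurement on stored photographs, with no extra visits. The downside is that absolute values are slightly biased away from zero for patients close to neutral.
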